### Safety Management

Given the high suicidality in BDD (19), we aim to provide a thorough safety management in our study. First, potential participants with concrete suicidal intentions and plans identified during screening and/or diagnostic sessions will be excluded from participation and will be informed about potential places to seek treatment in their area of residence. During the intervention, we will have a weekly monitoring of suicidal ideation in place, which the study therapist has to consult prior to interaction with the patient. If suicidal ideation develops, a stepped-care plan will be set in motion, including anti-suicide contracts, a telephone call with the study therapist in which a stepped emergency plan is developed, a telephone call with the supervisor (AH; a clinical psychologist with expertise in treatment of BDD), and involvement of treatment providers in the patient's area of residence. In order to track the general development of all patients, a fortnightly supervision session will be held. The supervisor will be accessible for the study therapist during the whole project. For *post-hoc* analyses, we will also assess adverse events during and after the intervention (see measures) to assess its moderation of treatment effects.

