### Assessment and Data Management

Detailed self-reports will take place at screening (t0), baseline (t1) prior to randomization, mid-intervention (t2), post-intervention (t3), and 4-week follow-up (t4; see Figure 1 for a detailed overview). On a more regular basis, we will gather brief self-reports on suicidal intent and negative emotions (after each session) as well as on BDD and depressive symptoms (after each module). Self-reported data (t0 through t4) will be collected using the secure online-based assessment system Unipark (EFS Survey, Questback GmbH, Cologne). Expert interviews will be conducted over the internet at t1 and t3 *via* the secure online video conferencing platform RedConnect (RED Medical Systems GmbH, Munich).

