**Intervention-related measures**											
Credibility/expectancy questionnaire^Q^	(68)	Treatment expectancy and rationale credibility	6	Expectancy; Credibility	9-point Likert scale from 1 (*not at all*) to 9 (*very*) and 11-point Likert scale from 0 to 100%	0.84–0.85		x		x	x
Technology affinity questionnaire^g^^,^^Q^	(69)	Technological affinity	19	Excitement; positive consequences; negative consequences; competence	5-point Likert scale from 0 (*not at all true*) to 4 (*exactly true*)	0.73–0.86	x			x	x
Adverse events^Q^	Adapted from (70)	Adverse events due to intervention	3	−	Yes/no; 4-point Likert scale from 0 *(not at all)* to 3 *(very strongly)*	−			x	x	x
Client satisfaction questionnaire, adapted for inpatient fields of work^h^^,^^Q^	(71)	Patient satisfaction	8	−	4-point Likert scale with scale content depending on the item [e.g., 1 (*excellent*) to 4 (*bad*)]	0.87–0.93			x	x	
Message credibility scale^Q^	(72, 73)	Program and therapist credibility	3	−	7-point Likert scale from 1 (*very badly*) to 7 (*very well*)	0.87			x	x	
Working alliance inventory—short revised^Q^	(74–76)	Therapeutic alliance	12	–	5-point Likert scale from 1 (*rarely*) to 5 (*always*)	0.81–0.91			x	x	

Q *Self-report Questionnaire*;

I *Semi-structured Interview*;

*^a−h^Translated from German-language original*:

a *Fragebogen Körperdysmorpher Kognitionen*;

b *Fragebogen zum Körperbild*;

c *Diagnostisches Kurzinterview bei psychischen Störungen*;

d *Fragebogen zu sozialer Angst und sozialen Kompetenzdefiziten – Version für Jugendliche*;

e *Ruminations-Suppressions-Fragebogen*;

f *Fragebogen zur Erfassung der Technikaffinität*;

g *Fragebogen zur Lebensqualität von Kindern und Jugendlichen − Revidierte Form*;

h *Fragebogen zur Messung der Patientenzufriedenheit*;

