#### Feasibility and Acceptability Outcomes

Feasibility and acceptability will be measured using the instruments highlighted in dark gray in Table 2.

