### Statistical Methods

All statistical analyses will be conducted using SPSS Statistics (IBM; Armonk, New York, USA) and R (77). Data will be mainly analyzed on an intention-to-treat basis including all randomized participants irrespective of their completion of the intervention. Additionally, study completer analyses including only participants who completed the post-intervention questionnaire battery and interviews will be conducted. Missing data will be imputed. Dropouts and completers will be compared with respect to study variables.

The main analysis focusing on efficacy of ImaginYouth will be analyzed using a repeated measures analysis of variance (rmANOVA) comparing pre- to post- intervention scores of the primary outcome. For the main analysis focusing on superiority of ImaginYouth over the SOT intervention, we will conduct a rmANOVA in the primary outcome between the two intervention conditions and changes from pre- to post-intervention. *Post-hoc t*-tests will be used to examine main effects or interactions in more detail. Cohen's d will be reported as a measure of effect size.

Secondary analyses include the examination of categorical hypotheses [e.g., for the examination of differences between ImaginYouth and SOT in responder (defined as an empirically derived cut-off point of ≥30% reduction from baseline on the BDD-YBOCS), and remission rates (operationalized as a BDD-YBOCS score ≤16 (42))] at post-intervention using Fisher's exact test. Hypotheses on efficacy and superiority regarding self-reported BDD-symptoms severity and associated (comorbid) symptoms will also be tested rmANOVAs (see above). Stability over the follow-up period and differences therein between ImaginYouth and SOT will be tested using a rmANOVA comparing pre-intervention to follow-up scores of self-reported BDD symptom severity. Finally, to examine the feasibility and acceptability of the intervention, the respective measures will be inspected descriptively.

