### Sample Size Calculation

Our a priori power analysis using G^*^Power (78) focused on the main hypothesis of a greater reduction of BDD symptoms in the main outcome measure from pre- to post-intervention in the ImaginYouth than in the SOT group. Thus, we calculated the number of participants necessary to test the interaction effect in a 2 (intervention type) × 2 (repeated measures assessment point) analysis of variance.

The power analysis was based on α= 0.05 and 1-β= 0.95, and an effect size of *f* = 0.36 [yielded by a meta-analysis on effects in internet-based intervention studies in youth by (32)]. The resulting total sample size is *n* = 28. Taking into account expected dropouts [about 30% in internet-based studies; (79)], we aim to recruit 20 patients per study arm type.

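### Adverse events, recorded only after randomisation and defined as due to the intervention, are named as a moderator of the treatment effect; that post-hoc analysis is open to bias

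*Protocol article*

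**What the plan says.** The protocol article's Safety Management section gives a purpose for the adverse-event data: for post-hoc analyses, "we will also assess adverse events during and after the intervention (see measures) to assess its moderation of treatment effects".

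Table 2, under the intervention-related measures, describes the instrument as a three-item self-report questionnaire with yes/no answers and a rating from 0 to 3. Its construct is "Adverse events due to intervention". The row carries three time-point marks, which read as t2, t3 and t4, with none at screening or baseline.

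Assessment and Data Management fixes the order of events: "baseline (t1) prior to randomization, mid-intervention (t2), post-intervention (t3), and 4-week follow-up". Expert interviews take place at t1 and t3 only, and the abstract names post-intervention as the primary endpoint.

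Two further sentences bear on how these data may be reported. Under Feasibility and Acceptability Outcomes, "Feasibility and acceptability will be measured using the instruments highlighted in dark gray in Table 2". Under Statistical Methods, for feasibility and acceptability, "the respective measures will be inspected descriptively".

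**The concern.** A moderator has to be fixed before treatment starts, so that within each of its levels the two arms are still comparable by randomisation. This variable does not qualify, for three reasons.

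- **It is a consequence of treatment by definition.** Its construct is harm attributed to the intervention. The content of the two arms also differs: Table 1 lists exposure and mirror-exposure homework for ImaginYouth, whereas the supportive condition offers the first module's reading material without exercises, plus messages. An event due to the intervention need not mean the same thing in each arm.
- **Part of it is measured too late.** Reports at t3 coincide with the primary outcome and reports at t4 follow it. At those points, how a participant has fared may influence the report.
- **It is self-reported.** Participants who are doing badly may plausibly report more events whatever their arm.

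At stake is a secondary message from a 40-patient trial about whom the programme helps. A statement that the benefit is larger, or smaller, in participants with adverse events could arise from selection alone.

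**Working it through.** **The plan's own figure.** The documents state no number for adverse events or for the moderation analysis. The only quantitative anchor is the sample size: "The power analysis was based on α= 0.05 and 1-β= 0.95", with "an effect size of *f* = 0.36" and dropout of "about 30% in internet-based studies". For the 2 × 2 interaction, λ = f²·N·m/(1 − ρ) with m = 2 and df = 1 and N − 2. The documents give no ρ; with ρ = 0.5 assumed, λ = 0.36² × 28 × 2/0.5 = 14.5. This gives power 0.956 at N = 28, against 0.941 at N = 26. Then 28/(1 − 0.30) = 40. Both figures reproduce, and the present point does not change them. The value d = 2f = 0.72 is used below only as a convenient uniform true effect.

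**Check 1: closed form, events track prognosis equally in both arms.** Assumed: event rates of 40% (ImaginYouth) and 20% (supportive), and a latent correlation r = 0.5 between event propensity and poorer outcome. Let c be the normal cut-off with Φ(c) = 1 − event rate.

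- Mean residual without an event, −r·φ(c)/Φ(c): −0.322 in ImaginYouth and −0.175 in the supportive arm; difference −0.147.
- Mean residual with an event, r·φ(c)/(1 − Φ(c)): 0.483 and 0.700; difference −0.217.
- Apparent benefit: 0.72 + 0.147 = 0.87 SD without events, and 0.72 + 0.217 = 0.94 SD with events.
- False interaction: 0.94 − 0.87 = 0.07 SD, with the larger apparent benefit in those with events.

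The effect is overstated in both strata, but the contrast between strata, which is what a moderation test examines, is small.

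**Check 2: simulation.** Change score = −0.72·arm + 0.6·U + 0.8·noise (SD 1 within arm; negative means improvement), where U is prognosis. For an average participant the event probability is 10% (supportive) and 30% (ImaginYouth). The change score is regressed on arm, event and arm × event. The true interaction is zero throughout. Effects and interactions below are from simulated trials of 4,000; false-positive rates are from 3,000 simulated trials of N = 40, among those where the model could be fitted.

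| Events depend on U | Effect, no event | Effect, event | Interaction | False positives, N = 40 (nominal 5%) |
|---|---|---|---|---|
| Not at all | −0.72 | −0.72 | 0.01 | 5.1% |
| Equally in both arms (log-odds 1 per SD) | −0.81 | −0.85 | −0.04 | 4.7% |
| In ImaginYouth only (log-odds 1 per SD) | −0.89 | −0.38 | 0.51 | 9.1% |
| In ImaginYouth only (log-odds 2 per SD) | −1.00 | −0.27 | 0.73 | 12.2% |

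In the two ImaginYouth-only rows at N = 40, about 12% of simulated trials (368 and 352 of 3,000) could not estimate the interaction because a cell was empty.

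**Reading.** With no shared cause there is no bias. With a shared cause that acts alike in both arms, the interaction is off by 0.04 to 0.07 SD. With a shared cause in one arm only, it is off by 0.51 to 0.73 SD and changes sign, so the benefit appears larger in those without events.

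**The case against.** The strongest reply is that the analysis is peripheral. It is labelled post-hoc and appears neither among the primary and secondary analyses in Statistical Methods nor in the sample size calculation. That stands: no main conclusion rests on it.

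A second reply is that bias is not inevitable and may be small. That also stands. It vanishes if events and outcome share no causes, and it is slight for the interaction if they are linked equally in both arms. The large figures need events to track prognosis in ImaginYouth only. The difference in arm content makes this conceivable, but the documents neither support nor refute it.

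A reader might go further and infer that no comparison of adverse events by arm is planned. The documents do not support that. The instruments counted as feasibility and acceptability measures are marked by dark-gray shading in Table 2, which is lost in the text available here. The adverse-event row may be among those to be described. An article may also leave adverse-event tables to the full protocol or analysis plan. For the same reason it cannot be confirmed that moderation is the only use intended.

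What the replies do not remove is the stated method. Calling the analysis post-hoc does not turn a post-randomisation, treatment-affected variable into a valid moderator.

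**Conclusion.** The point holds in a limited form. The article names as a moderator a variable that is measured only after randomisation, is defined as due to treatment, and is partly recorded at or after the primary endpoint. Stratifying on it, or testing an interaction with it, gives up the protection of randomisation and is open to bias when events share causes with outcome.

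Neither the size nor the direction follows from the documents, which give no event rates and no link between events and outcome. Under the assumptions shown, the spurious interaction runs from none, through about 0.04 to 0.07 SD, to about 0.5 to 0.7 SD in the other direction. The reading of the time points as t2 to t4 rests on the layout of the extracted table, but it agrees with the wording in Safety Management. The primary comparison, its power and the sample size are untouched.

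**What to change.** Replace the moderation sentence in Safety Management with three statements.

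1. Adverse events are described by arm as a safety outcome: the number and proportion of participants with any event, and with severe ratings, at each of t2, t3 and t4. The category of the 0 to 3 rating that counts as severe is set beforehand. The number who responded is shown at each time point, and non-responders are not counted as event-free. This matters because, with the expected 30% dropout, about 20 × 0.70 = 14 per arm would report. If, say, 4 of those 14 had an event, the proportion is 29%; dividing by all 20 randomised would show 20%.
2. Moderator analyses are limited to variables measured before randomisation.
3. Any association between adverse events and outcome is labelled exploratory and non-causal.

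Cost: one sentence and one descriptive table, on data already being collected and with no change in sample size. The trial gives up a moderation claim that it could not validly make.

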### Quality Management

Quality management (i.e., adherence to condition and engagement) will include the aforementioned fortnightly supervision session, measurement of the time used to communicate with each patient as well as number of messages. Messages between patients and study therapist are in written format only, are recorded, and can be subject to content analysis of adherence to condition during data analysis. Furthermore, diagnostic sessions will be recorded and interrater reliability will be calculated in 20% of randomly chosen cases. The diagnostician will be blind to the randomization of the participants and will be replaced if deblinded.

### Assessment and Data Management

Detailed self-reports will take place at screening (t0), baseline (t1) prior to randomization, mid-intervention (t2), post-intervention (t3), and 4-week follow-up (t4; see Figure 1 for a detailed overview). On a more regular basis, we will gather brief self-reports on suicidal intent and negative emotions (after each session) as well as on BDD and depressive symptoms (after each module). Self-reported data (t0 through t4) will be collected using the secure online-based assessment system Unipark (EFS Survey, Questback GmbH, Cologne). Expert interviews will be conducted over the internet at t1 and t3 *via* the secure online video conferencing platform RedConnect (RED Medical Systems GmbH, Munich).

### Outcomes

#### Primary Outcomes

*Yale-Brown Obsessive-Compulsive Scale Modified for Body Dysmorphic Disorder* [BDD-YBOCS; (40); German version: (41)]. The main primary outcome assessing severity of BDD symptoms will be the semi-structured expert clinical interview BDD-YBOCS (40). This will also be used to assess responder and remission status (42). The BDD-YBOCS is the gold standard instrument and assesses both cognitive (e.g., time occupied by thoughts about body defect) and behavioral symptoms (e.g., degree of control over compulsive behavior) of BDD and delusionality using a total of 12 items. The item regarding delusionality will be rated again within the participants' answers on the Brown Assessment of Beliefs Scale [BABS; (43)]. Items on the BDD-YBOCS are rated on a 5-point Likert Scale from 0 to 4, with the scale content depending on the respective item (e.g., 0 = *none* to 4 = *extreme [spends more than 8 h/day on these activities]*). The scale has shown good internal consistency (0.80) and interrater reliability [0.99; (40)].

#### Secondary Outcomes

Detailed information on number of scales, items, content scaling, and psychometric properties of all secondary measures (both for further BDD-symptoms and comorbid psychopathology) included in this protocol and primary analyses are highlighted in light gray in Table 2. Table 2 also presents all other variables assessed in the study but not in the focus of the main analyses of the study. Some measures will be administered after each session and/or each module, which is indicated by superscripted post-module or post-session mention.

**Table 2 T2:** Description of instruments and psychometric characteristics as well as points of measurement.

**Instrument**	**Author (German-language version)**	**Construct**	**Number total items**	**Subscales**	**Scale**	**Cron bach‘s α**	**Time point**				
							**0**	**1**	**2**	**3**	**4**
**Secondary BDD symptoms**											
Body dysmorphic disorder diagnostic module^I^	KDS-Net (unpublished manuscript)	DSM-5 based Diagnosis of BDD	8	–	3-point scale 1 (not applicable), 2 (subclinically applicable), and 3 (present/applicable)	0.96		x		x	
Brown assessment of beliefs scale^I^	(43, 44)	Delusional appearance-related thoughts	7	–	5-point Likert scale with scale content depending on the item (e.g., 0 (*absolutely sure that belief is wrong)* to 4 (*absolutely sure that belief is correct)*	0.87		x		x	
Dysmorphic concern questionnaire^Q^^,^^Post−module^	(45, 46)	Severity of BDD symptoms	7	–	4-point Likert scale from 0 (*not at all*) to 3 (*much more than other people*)	0.85	x		x	x	x
Body dysmorphic symptoms inventory^Q^	(37)	Severity of BDD symptoms	18	Specific BDD symptoms; associated characteristics	5-point Likert scale from 0 (*not at all, never, do not think about it at all*) to 4 (*very strong, more than 5 times, more than 8 h per day*)	0.88	x		x	x	x
List of safety behaviors^Q^	Martin et al. (2021)	Number and extent of safety behaviors	30	–	5-point Likert scale from 1 (*never*) to 5 (*very often*)	–		x		x	x
Mirror gazing questionnaire^Q^	Adapted from (6)	Mirror gazing behavior	8	–	Scale and scale content depending on the item (e.g., *yes*/*no*)	–		x		x	x
Physical appearance comparison scale^Q^	(47, 48)	Body-related social comparison habits	5	–	5-point Likert scale from 1 (*never*) to 5 (*always*)	0.75		x		x	x
Questionnaire of body-dysmorphic cognitions^a^^,^^Q^	Stangier and Ritter (2015); unpublished manuscript	BDD-related cognitions	20	–	5-point Likert scale from 1 (*never*) to 5 (*always*)/scale from 0 (*not convinced*) to 100 (*totally convinced*)	–	x		x	x	x
Body image questionnaire^b^^,^^Q^	(49)	Body image	20	Negative body assessment; Vital body dynamics	5-point Likert scale from 1 (*not at all true*) to 5 (*very true*)	0.84–0.91		x		x	x

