### Participants and Procedures

#### Inclusion and Exclusion Criteria

Inclusion criteria include age between 15 and 21 years, a primary diagnosis of BDD (comorbid diagnoses are allowed) established by the expert interview Body Dysmorphic Disorder Diagnostic Module for DSM-5 [BDDDM; (36)] after a previous sum score of ≥14 on the Body Dysmorphic Symptoms Inventory [BDDI as is in the Table; (37)] during the screening. Exclusion criteria current substance abuse, bipolar or psychotic episodes, suicidal intent and plans, current psychotherapy, cognitive limitations that would hinder work on the intervention, and/or a change in psychopharmacological medication in the last 2 months.

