#### Assessment of Eligibility and Randomization

After participants have contacted us by telephone, email or via our social media channels, they will be provided with a link to the online self-report screening (t0, in Unipark; EFS Survey, Questback GmbH, Cologne) through a self-chosen email address. If they fulfill the first inclusion criteria (age, BDDI as is in Table sum score ≥14, and no current psychotherapy), the diagnostician (a clinical psychologist in training) will contact them by email in order to make an appointment to (1) conduct the informed consent procedure and (2) complete the structured clinical interviews. The diagnostician is blind to the condition of the participant both at pre- and post-assessment. In case of crossover (i.e., a participation in ImaginYouth after having participated in SOT before) the ratings will not be blind anymore. The diagnostician will also provide the participants with detailed written information on the study procedure, our privacy policy and a note that it is possible to withdraw from the intervention at any time without facing any consequences. The informed consent procedure and the interviews will be conducted online using RedConnect (RED Medical Systems GmbH, Munich), the latter only after the informed consent form has been sent to the diagnostician by email. If the participants fulfill the remaining inclusion and exclusion criteria, they will then be randomized to one of the two intervention conditions by our external collaboration partners (AM and KS) who, from this point, will not be further involved in the study. A full randomization of the prospective 40 cases will be generated via a list randomizer (RANDOM.ORG, Randomness and Integrity Services Ltd, Dublin) by KS. Once randomization has been conducted, the second first-author (MS; study therapist in both conditions; clinical psychologist in training) will provide participants with a log-in for the intervention to which they have been allocated on the e-mental-health platform Minddistrict (Minddistrict, Berlin).

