**Post−module:**
*after every completed module of the ImaginYouth condition and simultaneously in the Online supportive therapy condition; t0 = self-report screening, t1 diagnostic inteview (baseline), t2 = self-report assessment (mid-intervention), t3 = diagnostic Interview and self-report assessment (post-Intervention), self-report assessment (follow-up)*.

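### Self-reported BDD severity has no t1 value: its pre-treatment score is the screening score, and for the BDDI that is the eligibility score, so within-arm reductions include some regression to the mean

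*Protocol article*

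**What the plan says.** - **Entry.** Under Inclusion and Exclusion Criteria, the diagnosis is made by interview "after a previous sum score of ≥14 on the Body Dysmorphic Symptoms Inventory". Assessment of Eligibility and Randomization places this check in the online screening at t0, before consent, interview and randomisation: "If they fulfill the first inclusion criteria (age, BDDI as is in Table sum score ≥14, and no current psychotherapy".
- **Schedule.** Table 2 has two self-reports whose construct is severity of BDD symptoms, the "Dysmorphic concern questionnaire" (7 items) and the "Body dysmorphic symptoms inventory" (18 items scored 0 to 4). Both are ticked at t0, t2, t3 and t4, with t1 empty. The body-dysmorphic cognitions questionnaire (20 items) has the same pattern. Most other self-report outcomes are ticked at t1, t3 and t4.
- **Baseline.** Assessment and Data Management treats t1 as a self-report occasion: "Detailed self-reports will take place at screening (t0), baseline (t1) prior to randomization".
- **Analysis.** Statistical Methods says: "Hypotheses on efficacy and superiority regarding self-reported BDD-symptoms severity and associated (comorbid) symptoms will also be tested rmANOVAs". Efficacy there means change over time within ImaginYouth; superiority means the comparison with SOT. Stability at follow-up is tested by "comparing pre-intervention to follow-up scores of self-reported BDD symptom severity", and the same sentence covers differences between the arms. Expert interviews take place only at t1 and t3, so follow-up severity rests on self-report.

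**The concern.** The pre value in any analysis of the BDDI can only be the t0 score, and that score was required to be at least 14. Patients selected because a fallible score was high will on average score lower next time, even without treatment. A test of reduction within one arm cannot separate this fall from a treatment effect.

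This matters because the Aims state within-arm hypotheses in their own right: a reduction in ImaginYouth from pre to post, extended to self-reported severity, and a significant reduction from pre-intervention to follow-up. At follow-up no expert rating is available to check the self-report result.

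**Working it through.** **Stated figures.** The plan gives no figure on this point. Its sample size is not affected. The total of 28 reproduces with an assumed correlation of 0.5 between repeated measures (noncentrality 0.36² × 28 × 2 / 0.5 = 14.5, power 0.956), and 28 / 0.70 = 40 gives the 20 per arm used below.

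**Inputs from the documents.** Cut-off 14; BDDI range 0 to 72 (18 × 4); Cronbach's alpha 0.88; 20 patients per arm; two-sided alpha 0.05.

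**Assumptions.** The BDDI is normally distributed among applicants with SD 10 or 12 and mean 10 to 36. The retest correlation r is 0.6 to 0.88; the upper end borrows the alpha. There is no true change.

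**Formula.** With c = (14 − mean)/SD and λ = φ(c)/(1 − Φ(c)):
- expected spurious fall = (1 − r) × SD × λ
- SD of selected patients = SD × √(1 + cλ − λ²)

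**Worked case, mean 14, SD 12.** c = 0, so λ = 0.399/0.5 = 0.798 and SD × λ = 9.57. SD of selected patients = 12 × √(1 − 0.637) = 7.2.
- r = 0.70: 0.30 × 9.57 = 2.87 points, or 0.40 SD
- r = 0.88: 0.12 × 9.57 = 1.15 points, or 0.16 SD

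**Range.** The fall is shown in points, with SDs of selected patients in brackets.

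| Applicant mean | SD 10, r 0.6 | SD 12, r 0.6 | SD 12, r 0.70 | SD 12, r 0.88 |
|---|---|---|---|---|
| 10 | 4.28 (0.80) | 4.90 (0.75) | 3.68 (0.56) | 1.47 (0.22) |
| 14 | 3.19 (0.53) | 3.83 (0.53) | 2.87 (0.40) | 1.15 (0.16) |
| 20 | 1.84 (0.26) | 2.44 (0.29) | 1.83 (0.22) | 0.73 (0.09) |
| 28 | 0.65 (0.08) | 1.10 (0.11) | 0.83 (0.08) | 0.33 (0.03) |
| 36 | 0.14 (0.02) | 0.37 (0.03) | 0.28 (0.02) | 0.11 (0.01) |

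**False-positive rates.** These come from a simulation with no true change: SD 12, 20 per arm, 2,000 runs per setting. The within-arm test is a paired t-test. The between-arm test is a t-test on change scores, which is equivalent to the 2 × 2 interaction.

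| Applicant mean | Within arm, r 0.70 | Within arm, r 0.88 | Between arms, r 0.70 | Between arms, r 0.88 |
|---|---|---|---|---|
| 14 | 28.7% | 14.0% | 4.7% | 4.4% |
| 20 | 14.4% | 8.4% | 4.8% | 5.2% |
| 28 | 8.2% | 4.7% | 5.8% | 4.6% |
| 36 | 5.2% | 5.7% | 5.2% | 5.4% |

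The mean between-arm difference in change was within 0.07 points of zero in every setting.

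**DCQ.** It selects no one and regresses only through its correlation with the BDDI: (same-day correlation − later correlation) × λ. With assumed correlations of 0.7 to 0.8 falling to 0.5 to 0.6, the fall is 0.02 to 0.2 SD of the screened pool for applicant means of 28 down to 10.

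**With a t1 baseline.** A BDDI score taken after selection gives an expected fall from the cut-off of about zero, if the correlation with t0 is the same at t1 and later.

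**The case against.** The case for leaving the plan as it is has real force.

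- **Two severity scales exist.** A reader might infer that the selection score is the only pre-treatment self-report of severity. It is not: the DCQ is also taken at t0 and is not an entry criterion. What stands is that neither scale has a t1 value.
- **The BDDI's role is not certain.** Statistical Methods names no instrument for self-reported severity, and Secondary Outcomes identifies the main-analysis measures by shading in Table 2 that could not be read here; Figure 1 could not be read either. The point is therefore conditional on the BDDI being used.
- **The randomised comparison is sound.** A reader might infer that superiority, or the whole follow-up analysis, is biased. Both arms pass the same cut-off before randomisation, and the follow-up analysis also compares arms. The Discussion gives control of unspecific effects as an advantage of the active comparator. The BDD-YBOCS has its own t1 rating. This objection stands in full.
- **A long screening-to-baseline gap is not documented.** No interval between t0 and t1 is given, so neither its length nor a loss of precision from it can be asserted.
- **The size is assumed.** The larger figures require many applicants near 14 on a 0 to 72 scale. The later diagnostic interview would probably reduce the effect further.
- **A t1 value is not a full cure.** It removes regression caused by the cut-off, but not natural improvement in people who seek help when at their worst.

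None of this removes the regression from a within-arm BDDI claim measured from t0.

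**Conclusion.** The point holds in limited form. The BDDI, DCQ and cognitions questionnaire have only a screening value before treatment, and for the BDDI that value is the truncated eligibility score. If the BDDI enters the self-report severity analyses, its within-arm reductions to t3 and t4 include some regression to the mean.

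The size cannot be fixed from the documents. Under the stated assumptions it is about 0.2 to 0.5 SD of selected patients if applicants average near 14, with a within-arm false-positive rate of about 14 to 29% (SD 12, r 0.70 to 0.88, 20 per arm). It is negligible at 28 or above: at most 0.11 SD in the cases tabulated, with simulated rates of about 5 to 8%. The DCQ is affected only indirectly. The consequence is confined to secondary within-arm statements, but these include the stated hypothesis of a reduction sustained to follow-up.

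**What to change.** Add the BDDI, DCQ and cognitions questionnaire to the t1 self-report battery before randomisation. Use t1 as the pre value in the self-report analyses of these scales and keep t0 for eligibility only.

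For patients already enrolled without a t1 value, base BDDI conclusions on the between-arm contrast and make no within-arm efficacy or stability claim from t0.

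The cost is 18 + 7 + 20 = 45 items at an occasion where questionnaires are already given: a few extra minutes per patient and a small schedule amendment. Restricting the claims for patients already enrolled needs no further data.
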